**Exclusion criteria**
Participants suffering from comorbid conditions other than ADHD are excluded.Children whose parents are not willing to provide written consent for participation in the study are excluded.

All participants are comprehensively informed regarding the procedures of the study through a document named “Participant Information and Consent Form.” Moreover, the participants are informed about the purpose of the study as well as the following aspects of their participation:

Their participation is voluntary.They can ask questions about the study procedures before participating in the study.They will be aware of the underlying risk or burden associated with their participation.They will know who will benefit from conducting this research.They will know how data collection and data protection will be performed during the project’s lifetime as well as whether data will be destroyed or reused (in case there is a possibility to reuse them).They will be fully informed, and they will agree for further use of their data.They can leave the study at any time and withdraw their data from the study.They will be aware of the possible commercial exploitation of the research findings.

Each informed consent is signed by the researcher who informs the participant and the principal investigator of the study. The informed consent explicitly states that the study was approved by the Committee for Bioethics and Ethics of the Medical School at the Aristotle University of Thessaloniki and all personal details are anonymized using a unique user identification code.

### Ethics Approval

The study protocol (trial registration: NCT04362982) was approved by the Ethics and Bioethics Committee of the School of Medicine at the Aristotle University of Thessaloniki (reference number: 6.225/29.7.2020).

### Recruitment of Participants

We initially considered recruiting at least 20 participants (10 ADHD and 10 non-ADHD) in our pilot trials. We estimated the sample size for the definite study by performing power analysis using GPower software (version 3.1, Universität Düsseldorf). We conducted a paired *t* test analysis using a power of 0.8, a significance level of 0.05, and an effect size equal to 0.2. The total sample size was estimated to be 199 participants. As proposed by Billingham et al [28], the sample size in pilot trials does not need calculation but needs justification. Thus, recruiting a small number of participants seems sufficient according to the suggestions of Stallard [29] and is similar to what was proposed by Julious [30].

The ADHD group is mainly composed of patients from the Community Center for Mental Health of Children and Adolescents at the General Hospital of Thessaloniki “G. Papanikolaou,” which supports the implementation of pilot trials. Furthermore, dissemination activities such as social media posts, mass media interviews, information events open to the public, and project presentations at conferences and workshops are considered essential to recruit participants for pilot trials.

### ADHD360 Platform Design

The ADHD360 platform consists of 2 main components, a serious game and a mobile app for behavior monitoring.

#### Serious Game for ADHD

Game design covers a wide range of activities in designing games, including story, aesthetics, mechanics, and technology [31]. These variables have to be carefully considered for successful game design. Hunicke et al [32] propose the mechanics-dynamics-aesthetics framework and define game mechanics as the “mechanisms that describe the specific elements of the game, at the level of data presentation and algorithms (...), also the mechanics relate to the behaviors and control mechanisms provided to the player in the game context.”

The mechanics-dynamics-aesthetics framework standardizes the basic components of a game into distinct parts such as rules, systems, and fun. This distinction helps us in the design of the mechanisms because the basic components of the game can be translated into game design elements such as mechanics, dynamics, and aesthetics that are visible to both the end users and the game designer, but from different perspectives. There are some games that have been developed specifically to improve ADHD symptoms, whereas commercial game titles have also been used for research purposes to measure the performance of users with or without ADHD diagnosis [33].

The 2 games that focus on improving ADHD symptoms are Plan it Commander [34] and Antonyms [35]. The 2 major gaps in existing research are the (1) interconnection of the game mechanics with the diagnostic criteria according to DSM-V and (2) correlation of user performance with the standard results of ADHD tests through ML algorithms.

For bridging this gap, we focused on developing a serious game called “Pizza on Time” (Figure 1), which is a runner game. The player tries to avoid obstacles and collect coins to deliver the pizza, and each time the player hits an obstacle, a pizza slice is lost. When all the pizza slices are lost, the player needs to start over at the same level. There are 3 different in-game world levels (city, jungle, and space) with a total of 120 predefined sublevels. Additionally, 4 mini games were integrated with the main runner game to enrich the existing mechanics, retaining the concept of pizza delivery.

**Figure 1 figure1:**
[figure not shown]
Screenshot of the “Pizza on Time” game.

#### Mobile App for Behavior Monitoring

The ADHD360 monitoring app (mADHD360) developed in the project provides teachers, parents, and health professionals with features to easily monitor specific targeted behaviors related to ADHD. Although several related information and communications technology solutions were implemented to replace traditional pen-and-paper observation charts in the past years [24], not all of them were successful [6]. The mADHD360 app differs from other digital monitoring apps, which are mainly based on pre-existing traditional forms of assessment. Instead, the app addresses the need to include the range of observation features needed to conduct a complete functional behavioral assessment in a unique and an easy-to-use tool. Finally, it allows teachers, parents, and clinicians to use a sociocentric technology to create a network of people and develop and monitor a behavioral intervention plan that is shared among all people involved in the care of the child with ADHD.

The process of creating a new subject profile and monitoring behavior can be described as follows:

First, the associate user (usually one of the parents) creates an account and enters the basic data of the subject to be monitored in the mADHD360 app. There is a strict policy regarding the sensitive personal data of the children; it does not allow real names to be used or any other significant detail that can reveal the identity of the children in the real world.

The next step is to create a network of people, usually people that spend time with the child (such as a relative or a class teacher) and a health professional. The app supports a directory of ADHD experts, which can be added to the child’s observation network. Inviting other people is a very simple process, and it can be performed via email.

A limited number of ADHD-related behaviors are associated with the child. The associations come from a predefined vocabulary [36], but the user can also enter custom behaviors. The network of people can gather data to unveil the function of a child‘s behavior and plan an intervention to reduce or eliminate the undesirable behavior with the help of a health professional. Data are gathered in sessions, and for each behavior, the app can monitor the frequency and duration. Usually, there are 2 rounds of monitoring, 1 before the intervention and the other during or even after the intervention.

Finally, the efficacy of each treatment can be evaluated by health professionals through visual analysis of the data gathered by the network members during the assessment periods.

The mADHD360 app is based on the Web Health Application for ADHD Monitoring (WHAAM) [36]; although the basic principles are retained, the latter is enhanced with more features, such as asynchronous chat capabilities, and offers advanced usability and user experience.

From a technology point of view, the mADHD360 app is designed to run on mobile devices, smartphones, and tablets. It is delivered for free as a progressive web app with the main game.

### Analysis

#### Statistical Analysis

Statistical analysis is performed using SPSS (version 26.0, IBM Corp) and the statistical significance level is set at *P*=.05. Continuous variables are explored for normality by the Shapiro-Wilk test to calculate the appropriate descriptive statistics. Continuous variables that are approximately normally distributed are reported as means (SDs) whereas those that are not normally distributed as medians and IQRs (Q1-Q3, where Q1 and Q3 are the first and the third distribution quartiles, respectively). Neuropsychological data expressed as raw scores are treated as continuous variables. Categorical data are described as frequencies and percentages.

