### Neuropsychological Data

Neuropsychological data were obtained from 30 participants. They were evaluated using WISC-V by the psychologist of the ADHD360 team or by an approved national body within the last 2 years. Among the 30 participants, 10 (33%) were diagnosed with ADHD and 20 (67%) were considered as healthy controls (non-ADHD). There were 21 males (70%) and 9 females (30%). In the ADHD group, all participants were male, whereas in the non-ADHD group, 11 (55%) were male and 9 (45%) were female. The mean age of the screened participants was 11.40 (SD 2.85) years. In the ADHD group, the mean age of the participants was 12.90 (SD 2.64) years, whereas that of the participants in the non-ADHD group was 10.65 (SD 2.70) years.

According to the data from the first neuropsychological assessment, the mean score in the figure weights subtest in the ADHD group was 14.00 (SD 5.79), whereas the median score of this subtest in the non-ADHD group was 19 (IQR 13-24). The mean scores in the subtests block design, similarities, digit span, coding, and vocabulary are presented in Table 1.

The mean score of the participants in the inattention subscale of the ADHD Rating Scale-IV was 12.70 (SD 7.04), whereas that in the hyperactivity-impulsivity subscale was 10.97 (SD 6.65). In the full group of participants, the mean total score was 23.67 (SD 12.56). The mean scores on the ADHD Rating Scale-IV obtained by grouping the participants based on their diagnosis are presented in Table 2.

**Table 1 table1:** Mean scores of the study participants in the subtests block design, similarities, digit span, coding, and vocabulary.

WISC^a^ subtest	ADHD^b^, mean (SD)	non-ADHD, mean (SD)
Block design	19.60 (4.30)	22.85 (8.02)
Similarities	22.00 (7.45)	23.50 (9.05)
Digit Span	18.30 (4.03)	19.75 (6.26)
Coding	27.80 (9.69)	32.20 (13.46)
Vocabulary	20.20 (5.55)	23.05 (8.17)

^a^WISC: Wechsler Intelligence Scale for Children.

^b^ADHD: attention deficit hyperactivity disorder.

**Table 2 table2:** Mean scores of the participants on the ADHD Rating Scale-IV.

ADHD^a^ Rating Scale-IV	ADHD, mean (SD)	non-ADHD, mean (SD)
Inattention subscale	18.50 (5.84)	9.80 (5.74)
Hyperactivity-impulsivity subscale	15.30 (6.58)	8.80 (5.67)
Total score	33.80 (9.94)	18.60 (10.62)

^a^ADHD: attention deficit hyperactivity disorder.

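### The Shapiro-Wilk rule for choosing summaries does not require the same statistic in both groups, so figure weights is a mean in ADHD and a median in controls, with no exact like-for-like difference

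*Protocol article*

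**What the plan says.** The Statistical Analysis section sets the rule: "Continuous variables are explored for normality by the Shapiro-Wilk test to calculate the appropriate descriptive statistics". The consequence follows: "Continuous variables that are approximately normally distributed are reported as means (SDs) whereas those that are not normally distributed as medians and IQRs". For the level, "the statistical significance level is set at *P*=.05". The section does not say whether the test is run on the whole variable or within each group, nor that both groups must receive the same summary.

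The Neuropsychological Data section shows the rule in use. The group sizes are given as "Among the 30 participants, 10 (33%) were diagnosed with ADHD and 20 (67%) were considered as healthy controls (non-ADHD". For one subtest the smaller group has a mean: "the mean score in the figure weights subtest in the ADHD group was 14.00 (SD 5.79". The controls get a different statistic for the same subtest: "whereas the median score of this subtest in the non-ADHD group was 19 (IQR 13-24". Figure weights is absent from Table 1, and no control mean or ADHD median for it appears anywhere. For the rest, "The mean scores in the subtests block design, similarities, digit span, coding, and vocabulary are presented in Table 1", with a mean (SD) in both groups. The three ADHD Rating Scale-IV scores in Table 2 are also means (SDs) in both groups.

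The Results paragraph of the Abstract states that the initial neuropsychological assessment confirmed a deviation of the ADHD group.

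**The concern.** A table that describes two groups is there to be read across. When one group has a mean and the other a median, the visible gap mixes a difference between groups with whatever distance separates mean from median within a group. That happens here for the subtest where the groups look furthest apart.

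The rule invites a repeat. A normality test has less power in 10 children than in 20, so the same shape can pass in one group and fail in the other. The rule covers every continuous variable, and the In-Person Participation section repeats the assessment at the end of the study. Later scores could therefore be split between groups or between time points.

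**Working it through.** **Inputs.** Group sizes, figure weights, Table 1 and Table 2, all from Neuropsychological Data. Individual scores are not given, so the reported summaries cannot be reproduced directly.

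**Consistency check.** Means weighted by group size should return the stated overall means.
- Total: (10 × 33.80 + 20 × 18.60)/30 = 23.67
- Inattention: (10 × 18.50 + 20 × 9.80)/30 = 12.70
- Hyperactivity-impulsivity: (10 × 15.30 + 20 × 8.80)/30 = 10.97

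All three match, so group sizes of 10 and 20 apply.

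**Was the test run within group?** One decision for the whole variable would give either two means or two medians. Figure weights has one of each. Within-group testing is therefore an inference from the result; the article does not state it.

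**Subtest gaps (control minus ADHD).** The pooled SD is √[(9·SD₁² + 19·SD₂²)/28]. The Welch standard error is √(SD₁²/10 + SD₂²/20).

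| Subtest | Gap | % of control | Pooled-SD units | Welch 95% CI |
|---|---|---|---|---|
| Block design | 3.25 | 14 | 0.46 | -1.4 to 7.9 |
| Similarities | 1.50 | 6 | 0.18 | -5.0 to 8.0 |
| Digit span | 1.45 | 7 | 0.26 | -2.4 to 5.3 |
| Coding | 4.40 | 14 | 0.36 | -4.5 to 13.3 |
| Vocabulary | 2.85 | 12 | 0.38 | -2.4 to 8.1 |
| Figure weights (mean against median) | 5.00 | 26 | not exact | not exact |

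Figure weights has the largest apparent gap. All five comparable intervals include zero.

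**Approximate like-for-like gap for figure weights, assuming rough symmetry in the controls.**
- Control mean ≈ (13 + 19 + 24)/3 = 18.67. A version with optimal weights gives 18.64.
- Control SD ≈ (24 - 13)/(2 × 0.6267) = 8.78. Here 0.6267 is the normal quantile at (0.75 × 20 - 0.125)/(20 + 0.25).
- Gap ≈ 18.67 - 14.00 = 4.67.
- Standard error = √(5.79²/10 + 8.78²/20) = 2.68, with 25.6 degrees of freedom and t = 2.057.
- 95% CI ≈ 4.67 ± 5.52, or about -0.9 to 10.2. In pooled-SD units the gap is about 0.59.

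The gap exceeds that for coding only if the control mean is above 14.00 + 4.40 = 18.40. The approximation clears this by 0.27.

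**Bounds without a shape assumption.** The score range is not in the article and has to be assumed. Put each quarter of the 20 control scores (five children) at its lowest or highest possible value.
- Range 0-34: lowest mean (0 + 13 + 19 + 24)/4 = 14.0; highest (13 + 19 + 24 + 34)/4 = 22.5. The gap is 0 to 8.5.
- Range 5-30: lowest mean (5 + 13 + 19 + 24)/4 = 15.25; highest (13 + 19 + 24 + 30)/4 = 21.5. The gap is 1.25 to 7.5.

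**How often the rule splits a variable.** Shapiro-Wilk rejection at 0.05, by simulation, with the same shape in both groups. If a and b are the rejection rates at n=10 and n=20, the mismatch probability is a(1 - b) + b(1 - a).

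| Shape | n=10 | n=20 | Mismatch |
|---|---|---|---|
| Normal | 5% | 5% | about 9-10% |
| Gamma, skewness 1 | 14% | 29% | about 35% |
| Exponential, skewness 2 (severe) | 45% | 83% | about 53% |

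For skewed shapes the likelier mismatch is the one seen here. At skewness 1, a mean in the small group with a median in the large one has probability (1 - 0.14) × 0.29 ≈ 0.25; the reverse has 0.14 × (1 - 0.29) ≈ 0.10.

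**ADHD Rating Scale-IV total (ADHD minus control).** 33.80 - 18.60 = 15.2. The standard error is √(9.94²/10 + 10.62²/20) = 3.94, with 19.2 degrees of freedom and t = 2.091. The 95% CI is about 7.0 to 23.4. The pooled SD is 10.41, so the gap is about 1.46 pooled SD.

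**The case against.** The defence is largely right about scale. Choosing a descriptive summary by a normality test is a common convention. It drives no hypothesis test here, and the machine-learning pipeline uses gameplay features only. One score of nine is split: in the larger group, five of six subtests and all three rating-scale scores are still reported as means. Under rough symmetry, figure weights still ranks first. All of this stands.

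Three stronger readings are tempting and should be resisted.
- A reader might infer that the summary depends on group size rather than on the data. With eight of nine scores treated alike, the documents support only that group size contributes along with shape. Nor is a group of 10 passed as normal whatever its shape: a severe skew is rejected 45% of the time.
- A reader might take the 45% against 83% contrast as typical. It belongs to an exponential shape. The control quartiles lie 6 below and 5 above the median, so the central half shows no right skew. Skewness 1 (14% against 29%) is a milder illustration.
- A reader might infer that the abstract's deviation rests on figure weights and so falls. It does not: Table 2 is reported consistently and shows a clear difference.

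What survives is that the approximate gap needs near-symmetry in the very group that the stated rule must have judged non-normal. Without that assumption the size of the gap is open.

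**Conclusion.** The point holds as a minor reporting defect produced by a stated rule. The Shapiro-Wilk criterion lets the two groups receive different summaries, and for figure weights they did. No exact like-for-like difference or interval can be derived from the article. The estimate of about 4.7 (95% CI about -0.9 to 10.2) rests on rough symmetry in the controls; the wider bounds rest on assumed score ranges. That the test was applied within group is inferred from the result.

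The support for the abstract's statement is uneven. The rating scale shows a clear difference, whereas the five comparable WISC-V subtests are each compatible with none. All these intervals are unadjusted, and the groups differ in mean age (12.90 against 10.65 years) and sex (all male against 55% male). They describe these 30 children and do not isolate an effect of ADHD.

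**What to change.** 1. In Statistical Analysis, drop the normality test as the device for choosing summaries. Report mean (SD) and median (Q1-Q3) in both groups for every neuropsychological score, and move figure weights into Table 1.
2. Add a between-group difference with a 95% interval for each score, labelled descriptive and unadjusted because of the age and sex differences.
3. Where the abstract reports a deviation, say that it is supported by the ADHD Rating Scale-IV, and that the intervals for the five comparable WISC-V subtests include zero.
4. Apply the same reporting to the second assessment, so that groups and time points can be read across.

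The cost is a wider table and a few sentences. The scores of the 30 participants are already in hand, and no machine-learning result changes.

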**Results:**

A total of 43 participants were recruited for this study, where 18 were diagnosed with ADHD and the remaining 25 were controls. Initial neuropsychological assessment confirmed that the participants in the ADHD group showed a deviation from the participants without ADHD characteristics. A preliminary analysis of collected data consisting of 30 gameplay sessions showed that the trained ML models achieve high performance (ie, accuracy up to 0.85) in correctly predicting the users’ labels (ADHD or non-ADHD) from their gameplay session on the ADHD360 platform.

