#### In-Person Participation

The first part of the pilot study begins with a first meeting between the involved members of the research team and the parents of each participant at the Laboratory of Medical Physics and Digital Innovation, School of Medicine of Aristotle University of Thessaloniki (iMedPhys). The aim of this first meeting is to thoroughly inform the parents and the children regarding the nature and scope of the project, as well as the exact procedures that take place according to the research protocol. In this context, parents can ask questions, express any concerns regarding the project, and sign the informed consent form. Afterward, the participants are subjected to a brief neuropsychological assessment by an experienced psychologist from the research team. This neuropsychological assessment includes 6 subtests of the Wechsler Intelligence Scale for Children, Fifth Edition (WISC-V), an intelligence test that measures a child’s intellectual ability, and 5 cognitive domains that impact performance [26]. The 6 subtests of WISC-V used here are (1) similarities, (2) vocabulary, (3) block design, (4) figure weights, (5) digit span, and (6) coding. The main aim of this assessment is to obtain a more integrated view of the participants’ general intellectual abilities in several domains such as verbal comprehension, visual-spatial perception, working memory, processing speed, and fluid reasoning. The average time to complete the subtests is approximately 48-50 minutes. If any of the participants have been assessed by this scale during the past 2 years, they are not reassessed by our research team, and the children’s parents are kindly asked to provide the already existing scores of the aforementioned 6 subtests, if possible. Furthermore, the ADHD Rating Scale-IV [27] is a 4-point Likert brief questionnaire completed by the parents regarding the presence and frequency of ADHD symptoms. Inattention and hyperactivity-impulsivity are the 2 subscales integrated into the ADHD Rating Scale-IV. The total raw score of the scale is calculated by summing the scores of the 2 subscales.

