Subsequently, the participants interact with the serious game “Pizza on Time” that has been specifically developed for the ADHD360 project for approximately 30-45 minutes at iMedPhys. During this interaction with the serious game, a form is completed regarding the conditions, the duration and the behaviors that will possibly be occurred. Participants interact again with the serious game for 30-45 minutes at iMedPhys, continuing from the level at which they stopped at the previous visit to complete all the levels of the first setting (the urban setting).

After the aforementioned procedures, there is a telephone conversation between the participants’ parents and the psychologist who conducted the neuropsychological evaluation to discuss if there are any behaviors characteristic of ADHD that affect the daily functioning of the participants. Once the psychologist has reached a consensus with the parents that there are certain behaviors that could be observed, the behaviors are introduced into the participant's account in the mADHD360 app. Instructions regarding the installation and use of the mobile app are provided by the research team through email. The mADHD360 app can be used on a smartphone or tablet. An observation plan is scheduled, including at least 2-4 times per week of behavioral monitoring regarding the frequency or the duration of these behaviors during the time they usually spend with the participant. Each round of behavior monitoring has a duration of 12 minutes. The duration of this phase is determined to be 2 weeks. During the behavior monitoring phase, the participants do not interact with the serious game.

Once behavior monitoring is complete, the research team instructs the participants to continue playing the game using the second (jungle) and third (space) settings on the premises of iMedPhys. The mean duration of this part is 10 weeks with a frequency of at least 2 times a week, depending on the participants’ availability. In this second part of the pilot testing phase, the goal is to exploit the serious game as an intervention to improve certain ADHD symptoms.

Next, a second round of behavior monitoring is performed following the same procedures as the previous one. Furthermore, a neuropsychological assessment is conducted following the same procedures as those during the first evaluation in the beginning of their participation.

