**Inclusion criteria**
Participants should be between 7 and 16 years old.Participants of the attention deficit hyperactivity disorder (ADHD) group should be diagnosed by an approved body of the Ministry of Health.Participants should be willing to follow the study protocol and procedures.The ADHD symptoms should not be attributed to organic disease.Parents must voluntarily provide written consent for their child’s participation in the study.

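### WISC-V subtests are compared as raw scores between groups whose mean ages differ by 2.25 years, so Table 1 is open to confounding by age and probably understates the ADHD deficit

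*Protocol article*

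**What the plan says.** All references are to the protocol article.

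- **Scoring (Statistical Analysis).** "Neuropsychological data expressed as raw scores are treated as continuous variables". The section sets descriptive summaries only: mean and SD if approximately normal by the Shapiro-Wilk test, otherwise median and IQR. It mentions neither age-standardised scores nor age adjustment.
- **Age range (Inclusion criteria).** "Participants should be between 7 and 16 years old".
- **Observed ages (Neuropsychological Data).** "In the ADHD group, the mean age of the participants was 12.90 (SD 2.64) years", against 10.65 (SD 2.70) in the non-ADHD group; n = 10 and 20.
- **Entry scores (In-Person Participation).** "If any of the participants have been assessed by this scale during the past 2 years, they are not reassessed by our research team"; parents are asked for the existing scores instead. The Neuropsychological Data section confirms that the reported children were tested "by the psychologist of the ADHD360 team or by an approved national body within the last 2 years".
- **Final assessment (In-Person Participation).** After the game phase and the second monitoring round, "a neuropsychological assessment is conducted following the same procedures as those during the first evaluation".
- **Reported comparison.** Table 1 gives means and SDs by group for five subtests. For the sixth, figure weights, the text gives a mean of 14.00 (SD 5.79) in the ADHD group but a median of 19 (IQR 13-24) in the non-ADHD group.
- **Conclusion drawn (Abstract, Results).** "Initial neuropsychological assessment confirmed that the participants in the ADHD group showed a deviation" from the children without ADHD characteristics.

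**The concern.** A raw score on an ability test is not comparable between children of different ages if older children tend to score higher. The groups here are small, not randomised and not matched on age, and the ADHD group is clearly older. A raw-score comparison then mixes any effect of ADHD with the effect of being about two years older. At stake is whether Table 1 can be read as a cognitive comparison at all, and what the abstract may conclude from it.

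A second issue arises only if WISC-V change is analysed. A raw-score change measured from a test taken up to 2 years before entry includes development over that time as well as over the study.

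**Working it through.** **Step 1: reproduce the article's pooled age.** Inputs from Neuropsychological Data: ADHD 12.90 (SD 2.64), n = 10; non-ADHD 10.65 (SD 2.70), n = 20.

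- Mean = (10 × 12.90 + 20 × 10.65)/30 = 342/30 = 11.40.
- Within-group sum of squares = 9 × 2.64² + 19 × 2.70² = 201.24. Between-group = 10 × 1.50² + 20 × 0.75² = 33.75. SD = √(234.99/29) = 2.85.

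Both match the stated 11.40 (SD 2.85), so the group ages are internally consistent.

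**Step 2: size of the age imbalance.**

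- Difference = 12.90 − 10.65 = 2.25 years.
- Pooled SD = √(201.24/28) = 2.68; standardised difference = 2.25/2.68 = 0.84.
- Welch t = 2.25/√(2.64²/10 + 2.70²/20) = 2.25/1.03 = 2.18, p = 0.042. The pooled 95% CI is 0.12 to 4.38 years.

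**Step 3: Table 1 as reported, then adjusted for age under assumptions.** The documents give no relation between age and score, so the within-group correlation r is assumed at 0.3, 0.5 and 0.7, with a common linear slope:

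- slope per year = r × pooled score SD / 2.68
- adjusted difference = raw difference − slope × 2.25

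Worked example, block design at r = 0.5: pooled SD = √((9 × 4.30² + 19 × 8.02²)/28) = 7.04; slope = 0.5 × 7.04/2.68 = 1.31; adjusted = −3.25 − 1.31 × 2.25 = −6.2.

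| Subtest | ADHD − non-ADHD | Pooled SD | d | Welch p | r = 0.3 | r = 0.5 | r = 0.7 |
|---|---|---|---|---|---|---|---|
| Block design | −3.25 | 7.04 | −0.46 | 0.16 | −5.0 | −6.2 | −7.4 |
| Similarities | −1.50 | 8.57 | −0.18 | 0.63 | −3.7 | −5.1 | −6.5 |
| Digit span | −1.45 | 5.64 | −0.26 | 0.45 | −2.9 | −3.8 | −4.8 |
| Coding | −4.40 | 12.37 | −0.36 | 0.32 | −7.5 | −9.6 | −11.7 |
| Vocabulary | −2.85 | 7.43 | −0.38 | 0.27 | −4.7 | −6.0 | −7.2 |

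Every raw d is smaller than the age imbalance of 0.84. At r = 0.5 the standardised differences become −0.59 to −0.88.

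**Step 4: what supports the abstract.** None of the five Table 1 differences is significant on raw scores. The parent-completed ADHD Rating Scale-IV total (Table 2) differs by 33.80 − 18.60 = 15.20, Welch p about 0.001.

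**Step 5: re-used entry scores, relevant only to a pre-post comparison.** Two monitoring rounds of 2 weeks and a mean of 10 weeks of play give 2 + 10 + 2 = 14 weeks. On the same assumptions, development in between-child SDs is years × r/2.68:

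- over 2 years: 0.22 / 0.37 / 0.52 for r = 0.3 / 0.5 / 0.7
- over 14 weeks (14/52 year): 0.03 / 0.05 / 0.07

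The 2-year figure is the extreme for one child; the article gives no distribution of test dates.

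**The case against.** The case on the other side is substantial.

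- **Direction.** A reader might infer that age confounding manufactured the reported difference. The figures do not support this: the ADHD group is older yet scores lower on all five means, so correction would be expected to widen the gap. This stands.
- **Size.** That raw scores rise with age is an assumption, and the range above depends on it. This stands.
- **Pre-post bias.** A reader might infer that a planned WISC-V efficacy result is biased by maturation. No such analysis is stated. WISC-V is introduced to describe intellectual abilities, the paired t test in Recruitment of Participants names no outcome, and no follow-up scores are reported. This part is conditional.
- **Who has old scores.** A reader might suppose that re-used scores fall mainly in diagnosed children. The article gives no count in either group, so this cannot be claimed.
- **No final score.** Read literally, repeating the entry procedures would carry the 2-year exemption to the final visit and leave no retest. That reading is strained, because the text says an assessment is conducted then and the exemption concerns pre-existing scores. What remains is a need for clarification.
- **The abstract.** Its sentence does not mention WISC-V, and the rating scale, reported under the same heading, supports it. It is imprecise, not false.
- **Main goal.** The classifier uses gameplay features and the diagnostic label; no WISC-V score enters it.

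None of this removes the comparability problem: raw scores, a 7-16 age range and a 2.25-year gap are all in the text.

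**Conclusion.** The point holds for the group comparison. Followed as written, the plan sets raw WISC-V scores side by side in groups 0.84 SD apart in age, so Table 1 cannot be read as the difference associated with ADHD. If scores rise with age, the table probably understates the deficit: at assumed correlations of 0.3 to 0.7, differences of −1.45 to −4.40 become −2.9 to −11.7 across the five subtests.

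Three limits apply. The correlation is assumed. Table 1 does not label its score type; it is read as raw because the Statistical Analysis section names no other scale. The article also does not say whether the ages are at entry or at testing. If they are at entry, re-used scores could in the extreme put the gap at testing anywhere from 2.25 − 2 = 0.25 to 2.25 + 2 = 4.25 years, which is why age at testing is the quantity to use. Age is not the only imbalance: all 10 ADHD children are male, against 11 of 20 controls.

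The effect of old entry scores on WISC-V change is conditional on that analysis being done. The mixed summaries for figure weights and the abstract wording are minor reporting corrections. The classifier results and the sample size of 199 are not touched.

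**What to change.** 1. In Statistical Analysis, specify age-normed scaled scores for each WISC-V subtest, or raw scores adjusted for age at testing, and recompute Table 1. Cost: a table look-up or one covariate, plus the test date for each re-used score.
2. Use the same summary statistic in both groups for each subtest, for example median and IQR in both if either group is non-normal. Cost: none beyond retabulation.
3. If a pre-post WISC-V comparison is made, base it on age-normed scores and add a sensitivity analysis limited to children tested by the team at entry. Cost: fewer children in that analysis; the article does not give the number.
4. Reconcile the two statements in In-Person Participation, so that the 2-year exemption clearly applies at entry only and not at the final assessment. Cost: one clause.
5. In the abstract, attribute the deviation to the ADHD Rating Scale-IV. If an age-normed or age-adjusted WISC-V analysis later shows a difference, report it separately. Cost: one reworded sentence.
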